#### Cost savings to programmes

Analysis of cost savings to programmes of ready-made spectacles will only be undertaken if analysis of the primary outcome demonstrates non-inferiority. The unit cost of ready-made spectacles (Cost_Ready-made spectacles_) and custom spectacles (Cost_custom spectacles_) will be calculated. The cost of dispensing spectacles to the two groups of children in the study will be determined as follows:A = not eligible for the trial and dispensed custom spectaclesB = eligible for randomisation, that is, suitable for ready-made spectaclesThe cost of programmes without ready-made spectacles$$ \mathrm{C}\mathrm{o}\mathrm{s}{\mathrm{t}}^{\mathrm{Custom}\ \mathrm{o}\mathrm{nly}} = \mathrm{A}*\mathrm{C}\mathrm{o}\mathrm{s}{\mathrm{t}}^{\mathrm{Custom}} + \mathrm{B}*\mathrm{C}\mathrm{o}\mathrm{s}{\mathrm{t}}^{\mathrm{Custom}} $$The cost of programmes with ready-made spectacles$$ \mathrm{C}\mathrm{o}\mathrm{s}{\mathrm{t}}^{\mathrm{Ready}\hbox{-} \mathrm{made}\ \mathrm{used}} = \mathrm{A}*\mathrm{C}\mathrm{o}\mathrm{s}{\mathrm{t}}^{\mathrm{Custom}} + \mathrm{B}*\mathrm{C}\mathrm{o}\mathrm{s}{\mathrm{t}}^{\mathrm{Ready}\hbox{-} \mathrm{made}} $$The cost savings to programmes$$ \mathrm{C}\mathrm{o}\mathrm{s}{\mathrm{t}}^{\mathrm{Custom}\ \mathrm{o}\mathrm{nly}}\hbox{-}\ \mathrm{C}\mathrm{o}\mathrm{s}{\mathrm{t}}^{\mathrm{Ready}\hbox{-} \mathrm{made}\ \mathrm{used}} $$

#### Additional analyses

(i)*Reasons for non-spectacle wear*Reasons for non-wear will be compared in children who were not wearing ready-made spectacles or custom spectacles.(ii)*Predictors for spectacle wear*We will investigate factors that may affect spectacle wear in this cohort such as gender, age, degree of uncorrected refractive error in the better seeing eye, previously wore spectacles, and parental spectacle wear using multivariable logistic regression analysis.

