## Methods/design

The trial is a randomised, non-inferiority, double masked clinical trial of children with simple uncorrected refractive errors. A non-inferiority design was chosen, as the benefits of ready-made spectacles are the considerably lower cost and ease of dispensing, both of which have the potential to increase the efficiency and cost effectiveness of programmes. As millions of children are affected by uncorrected refractive errors, the lower cost of ready-made spectacles also has the potential to increase coverage of school-based programmes. Under these circumstances a slightly lower acceptance of ready-made spectacles, measured by spectacle wearing, might be acceptable. The non-inferiority margin of 10 % was chosen to balance the considerations of efficacy and secondary benefits. The allocation ratio is approximately 1:1.

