### Primary outcome

The primary outcome is the proportion of children who are wearing their spectacles at an unannounced visit to the school 3 to 4 months after delivery of the spectacles. A field worker, masked to the allocation arm, assesses spectacle wear using categories described by Wedner [13]. Categories 1 or 2 below are used to define spectacle wearing, and categories 3 or 4 as non-spectacle wearing:wearing the spectacles at the time of the unannounced visitnot wearing the spectacles at the time of the visit but have them at schoolnot wearing the spectacles at the time of the visit but said they are at homenot wearing the spectacles at the time of the visit as they are broken or lost

Children categorised as non-spectacle wearing are given an opportunity to give two reasons. The field worker asks the child the reason and this is coded and recorded on the follow-up data collection form.

Fieldwork has been planned such that the initial assessment, delivery of spectacles and follow-up 3 to 4 months later do not coincide with school examination periods, long school holidays, or the end of the school year when children may leave school.

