### Data analyses

Analysis will be in the groups to which the children were randomly allocated. We expect all children will have been given the correct spectacles. The randomisation code will only be broken once the analysis has been completed. We do not plan any subgroup analysis.

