### Harm

Inaccurate prescribing or fitting of spectacles can cause blurred vision and/or symptoms of eyestrain or headache whilst the spectacles are worn. All refractions in this trial will be undertaken by highly experienced optometrists, and so inaccurate prescribing is highly unlikely. In addition, children who have refractive errors not suitable for ready-made spectacles will not be eligible for the trial, thus reducing the risk of symptoms arising through under/over correction.

Children will not be specifically asked whether they have these symptoms but will be offered the opportunity to say whether symptoms were the reason why they discontinued wearing spectacles at the time of the unannounced follow-up visit. Any child who says that blurred vision, eyestrain or headaches were why they did not wear their spectacles will be refracted again and given a new pair of spectacles, if required.

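### Comparing reasons only among non-wearers can understate or reverse an excess of symptom-related non-wear on ready-made spectacles; report it per child randomised as well

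*Protocol article*

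**What the plan says.** Four parts of the protocol article bear on this.

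- **Analysis set.** Additional analyses, item (i): "Reasons for non-wear will be compared in children who were not wearing ready-made spectacles or custom spectacles".
- **Who gives reasons.** Primary outcome: "Children categorised as non-spectacle wearing are given an opportunity to give two reasons". The same section sets the split: "Categories 1 or 2 below are used to define spectacle wearing, and categories 3 or 4 as non-spectacle wearing". A child whose spectacles are at school but not on the face therefore counts as a wearer and is not asked.
- **Where symptoms enter.** The Harm section names the symptoms: "Inaccurate prescribing or fitting of spectacles can cause blurred vision and/or symptoms of eyestrain or headache whilst the spectacles are worn". It then states "Children will not be specifically asked whether they have these symptoms", and that at the follow-up visit they "will be offered the opportunity to say whether symptoms were the reason why they discontinued wearing spectacles".
- **General principle.** Data analyses: "Analysis will be in the groups to which the children were randomly allocated".

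The article describes no comparison of symptom-related non-wear over all randomised or all followed-up children.

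**The concern.** The children compared in item (i) are those who failed the primary outcome. If allocation affects wear, the two sets of non-wearers are not randomised groups, and the share citing a given reason depends on how many children stopped for every other reason. Suppose ready-made spectacles led more children to stop because of blurred vision, eyestrain or headache, and also led more to stop for unrelated reasons. The larger denominator would dilute the symptom share, and the arms could look alike or the ready-made arm could look better.

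The article foresees unequal wear: its Methods/design section accepts slightly lower wear with ready-made spectacles and states "The non-inferiority margin of 10 % was chosen to balance the considerations of efficacy and secondary benefits". At stake is how the only between-arm information on symptoms will be read. The primary risk difference is not at stake.

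**Working it through.** **Inputs from the article.** Reasons come from categories 3 and 4 only (Primary outcome). The margin is 10 percentage points (Methods/design). Planned size is 240–260 per arm, calculated one-sided with significance level 0.05 and 90% power (Sample size calculation). The article gives no figure for the reasons comparison, so there is none to reproduce.

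**Assumed input.** The article states no expected wear rate. I use 80% custom wear with 240 per arm, and show other rates in step 4. The planned size makes 80% a reasonable choice. With equal wear p in both arms, n per arm = 2p(1−p)(1.645+1.282)²/0.10². At p = 0.82 this gives 253, and 240–260 corresponds to p of about 81.3–83.2% (or the mirror values, 17–19%). At one-sided 0.025 it would be about 85.5–86.9%. Symptom counts below are also assumptions.

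**Step 1, the identity.** In each arm:

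P(symptom-related non-wear) = P(non-wear) × P(symptom reason given non-wear).

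Dividing ready-made by custom:

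ratio among non-wearers = (risk ratio over all randomised) ÷ (risk ratio for non-wear).

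An excess disappears when the two risk ratios on the right are equal, and reverses when the non-wear ratio is the larger.

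**Step 2, the mechanism at its clearest.** Wear of 80% versus 70% gives 240 × 0.20 = 48 custom and 240 × 0.30 = 72 ready-made non-wearers, a non-wear ratio of 1.50.

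| Symptom-related non-wear, custom vs ready-made | Per child randomised | Among non-wearers |
|---|---|---|
| 12 vs 18 | 5.0% vs 7.5% (ratio 1.50) | 25.0% vs 25.0% |
| 12 vs 16 | 5.0% vs 6.7% (ratio 1.33) | 25.0% vs 22.2% |

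**Step 3, whether that case would pass the primary test.** The wear deficit is 10 points, with standard error √[(0.8×0.2 + 0.7×0.3)/240] = 0.0393 and 95% CI 2.3 to 17.7 points. Non-inferiority fails. Step 2 shows the mechanism, not the size to expect in a successful trial.

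**Step 4, how large the distortion can be when non-inferiority is met.** The largest observed deficit d that still meets the margin solves d + 1.96 × √[(p(1−p) + (p−d)(1−p+d))/240] = 0.10. At p = 0.80, d is about 2.7 points and the non-wear ratio is 0.2267/0.20 = 1.13. With a 90% CI (1.645 in place of 1.96), d is about 3.8 points and the ratio 1.19.

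| Assumed custom wear | Largest non-wear ratio, 95% CI | Largest non-wear ratio, 90% CI |
|---|---|---|
| 50% | 1.02 | 1.05 |
| 70% | 1.06 | 1.10 |
| 80% | 1.13 | 1.19 |
| 90% | about 1.4 | about 1.5 |

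In whole children at 80% (95% CI), the largest passing case is 54 versus 48 non-wearers (ratio 1.125). Against 12 symptom-related non-wearers on custom:

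- 13 on ready-made is 5.4% versus 5.0% per child randomised, but 13/54 = 24.1% versus 25.0% among non-wearers: reversed.
- 14 on ready-made is 5.8% versus 5.0% (ratio 1.17), and 14/54 = 25.9% versus 25.0% (ratio 1.04): attenuated.

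**Step 5, when there is no masking.** With equal non-wear the two ratios in step 1 coincide. If all the extra non-wear is due to symptoms, the share rises: six extra children, all citing symptoms, give 18/54 = 33.3% versus 12/48 = 25.0%, and the signal shows.

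**The case against.** The strongest reply is that item (i) is an additional, descriptive analysis of reasons in general. The Background lists teasing, breakage, loss and dislike among them. Item (i) names no symptom, the Harm section announces no between-arm test, and asking why non-wearers do not wear their spectacles naturally means looking at non-wearers. If counts by reason are published, a reader can work out the per-child figure. Most of this stands, and it limits the point to a supplementary comparison. It does not remove the point: the article says reasons will be compared and names the set, and that set is the only route by which symptoms reach a comparison. The rule on analysis by allocated group fixes the arms, not this denominator.

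A second reply concerns size, and it stands. A reader might infer that the plan could give false reassurance used to justify programme-wide use of ready-made spectacles. The documents do not support that. Large masking needs a wear gap like that in step 2, which fails non-inferiority, and under Cost savings to programmes the savings analysis would then not be done.

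A reader might also infer that the bias reassures whenever ready-made wear is worse. Step 5 shows otherwise.

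Finally, the remedy would not settle differences of this size. For 12 versus 18 of 240, the risk difference is 2.5 points (95% CI −1.8 to 6.8). For 12 versus 16 it is 1.7 points (−2.5 to 5.9). That stands as a limit on precision; it is no reason to prefer the distorted denominator.

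**Conclusion.** The point holds in a limited form. The stated analysis set conditions the only between-arm symptom contrast on the post-randomisation primary outcome. That contrast can understate or reverse an excess of symptom-related non-wear on ready-made spectacles, provided non-wear for other reasons is also higher in that arm.

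In a trial that meets non-inferiority the effect is likely modest: division by a non-wear ratio of at most about 1.13, assuming 80% custom wear, 240 per arm, complete follow-up and a 95% CI. It is smaller at the lower wear rates of about 26–52% that the Background cites from two earlier trials, and larger only if wear is near 90%.

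A reader might take the comparison, or its replacement, to show how often each type of spectacles causes symptoms. Neither does. Children are not specifically asked about symptoms, and those who keep wearing their spectacles despite symptoms, or who have them at school, give no reasons.

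**What to change.** Keep the breakdown of reasons among non-wearers, marked as descriptive. Add, by allocated arm, the proportion of all children randomised who were classed as non-wearing and cited blurred vision, eyestrain or headache in either of their two reasons, with the risk difference and its 95% CI. If children assessed at the visit are used as the denominator instead, show the number missing in each arm. Name this as the between-arm comparison, call it symptom-related non-wear and not a symptom rate, and state that its precision will be low.

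The cost is a sentence or two of analysis text and one table row. The reasons are already coded on the follow-up form, so no new data are needed.

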### Data monitoring

A data monitoring committee will not be required, as both the intervention and comparator arms are not novel procedures and are in common use. There is no reason to expect significant adverse effects. Interim and subgroup analyses are not planned, and there will be no stopping rules.

### Harm

Inaccurate prescribing or fitting of spectacles can cause blurred vision and/or symptoms of eyestrain or headache whilst the spectacles are worn. All refractions in this trial will be undertaken by highly experienced optometrists, and so inaccurate prescribing is highly unlikely. In addition, children who have refractive errors not suitable for ready-made spectacles will not be eligible for the trial, thus reducing the risk of symptoms arising through under/over correction.

Children will not be specifically asked whether they have these symptoms but will be offered the opportunity to say whether symptoms were the reason why they discontinued wearing spectacles at the time of the unannounced follow-up visit. Any child who says that blurred vision, eyestrain or headaches were why they did not wear their spectacles will be refracted again and given a new pair of spectacles, if required.

### Ethics and dissemination

Ethical approval has been obtained from the Interventions Research Ethics Committee, LSHTM and the Institutional Review Board of Sankara Eye Institute. All investigators will contribute to the dissemination strategy, which is likely to include a summary of the findings for head teachers, a report for the website of both institutions, publications in peer-reviewed journals, presentation at national (UK and India) and international conferences.

### Protocol amendment

No important protocol modifications, such as changes to eligibility criteria, were required.

### Consent

Written informed approval has been obtained in the local language by the lead collaborator in India from each school authority, head teacher and/or the school administrator to allow the school to participate in the study. Written informed consent is being obtained from parents of children recruited to the trial. Parents of the children are being sent an information sheet which explains the study procedure along with the consent form in the local language.

Guidelines are being followed for school screening in India and by the collaborating institute which state that before starting screening at each school, children should be given verbal information about the study and an explanation of the procedures by trained field workers, which allows children to ask questions.

### Confidentiality

Data are kept confidential and no identifiers are entered into the databases. Data are anonymised by allocating a unique study ID for each participant. The unique study ID will be used to merge the two study datasets.

Paper records are being stored in a locked filing cabinet at LSHTM, and the data will be made readily available in a public domain after the initial analyses and results are published. At the end of the study, the data will be archived at LSHTM.

### Access to data

A memorandum of understanding has been drawn up between the two institutions highlighting intellectual property issues, which include data sharing and making the database available online.

### Post-trial care

It is recommended that school vision testing be repeated every two years, to identify children whose spectacles need to be replaced as well as to screen children aged 11–12 years for the first time. This will be discussed with head teachers, who may want to consider training teachers to measure visual acuity, with support from Sankara Eye Hospital. This is the process adopted in other schools in the locality.

## Discussion

This trial is designed to investigate whether low-cost, high-quality, ready-made spectacles result in comparable rates of spectacle wear at 3 to 4 months as more expensive custom spectacles and how much cost savings there would be to programmes.

The dissemination strategy will include a summary of the findings for head teachers, a report for the websites of both institutions, publications in peer-reviewed journals and presentations at national (UK and India) and international conferences. In India the findings will be shared with the State Ministry of Health, State Ministry of Education and specifically the Government of India’s ’Rashtriya Bal Swasthya Karyakram’ (RBSK) programme, which includes refractive error, technically called the ‘Child Health Screening and Early Intervention Services’.

### Trial status

At the time of submission recruitment was ongoing. Recruitment started on 12 January 2015 and ended on 31 July 2015. A total of 23,345 children were screened and 460 recruited.

## Abbreviation

D: dioptres
